**3.4. Study duration**

If a treatment centre treats about 500 late-stage patients annually, allowing for the inclusion criteria, which restrict the potential recruitment, it may be estimated that patient recruitment to the study will be completed within a maximum of 12 months. As the patients are followed up subsequently for 24 months, the total study duration is estimated at 36 months.

**3.5. Randomisation**

Patients will be randomised on D1 (inclusion date), the day on which treatment is initiated. A fixed randomisation method will be used: the probability of being assigned one or other treatment will remain constant throughout the study.

The patients’ demographic, laboratory or clinical features might change during the study because of the control programme in progress. A blocking process in the randomisation will ensure that a comparable number of patients is included in each group at all times. The blocking procedure will not be disclosed to the field team before the end of the enrolment period.

**3.6. Treatment and allocation**

Depending on their group, subjects will receive one of the treatment protocols. Patients will be treated from D1 onwards.

## Blind

The modes of administration of melarsoprol (direct IV), nifurtimox (orally) and eflornithine
(2-hour infusion) are different. A blind study is therefore not readily feasible under field conditions.

## Concomitant medications for the three groups

To improve the general fitness, all patients enrolled will be pre-treated with :

- Albendazole. To be prescribed systematically at the beginning of hospitalisation at the current protocol.
- An anti-malaria treatment with the current protocol

Metronidazole (Flagylâ) will not be used throughout hospitalisation because its side effects are the same as that of nifurtimox. If necessary, Metronidazole, Praziquantel, Ivermectine and Thiabendazole will be administered at the end of hospitalisation.

## Serum and CSF samples

A new diagnosis test is currently being developed by Antwerp Institute of Tropical Medicine. This novel tool is stage-specific and allows to follow up patients by quantitative determination of IgM in CSF. In order to collaborate in this research, samples of serum (2 tubes of 2 cc) and CSF (2 tubes of 2 cc) will be taken and then frozen immediately before and after the end of treatment. Assays of specific IgM will be performed in Europe (Antwerp Institute of Tropical Medicine).

***Melarsoprol***

Prednisolone will be co-administered systematically to patients included in groups A and B. Treatment with prednisolone will start 24 hours before the beginning of the course of melarsoprol and continued at decreasing doses of 1 mg/kg/day from D1 to D5 and 0.5 mg/kg/day from D6 to D11.

Melarsoprol will be co-administered systematically with another drug. A simplified protocol of a single series of 10 injections of melarsoprol will be used because of this combination. Patients will receive a dose of 1.8 mg/kg/day for 10 days.

## Eflornithine

Patients will receive the dosage currently used in the NSSCP/MSF Uganda programme of 100 mg/kg every 6 hours (given in a 2-hour infusion) for 7 days.

## Nifurtimox

Nifurtimox is administered orally. Dosage will be the same as that currently used in the programme for some patients, i.e.: 15 mg/kg/day for 10 days in adults and 20 mg/kg/day for 10 days in children under 15 years of age, divided in 3 doses per day.

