## Inclusion criteria

All patients suffering from *Tbg* HAT, with the following criteria:

- confirmed second-stage *T.b. gambiense* infection :
- Infection diagnosed parasitologically (blood or lymph node fluid) and white blood cells > 5/mm3 in cerebrospinal fluid (CSF)
- or Trypanosomes detected in the CSF [[1]](#footnote-2) with any CSF cell count
- and resident in the district
- and written consent of the patient or of one of the parents/guardians for children under 15 years of age.

The laboratory tests must have been carried out within the previous 14 days to be valid.

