***Dosage by treatment group***

**Table 1 : Timetable of treatment**

|  | **A** | | **B** | | **C** | |
| --- | --- | --- | --- | --- | --- | --- |
|  | **melarsoprol 1 inf / day** | **nifurtimox tabs 3/day** | **melarsoprol 1 inf / day** | **eflornithine 4 inf / day** | **eflornithine 4 inf / day** | **nifurtimox  tabs 3/day** |
| **D2** | 1.8 mg/kg | 15 mg/kg | 1.8 mg/kg | 400 mg/kg | 400 mg/kg | 15 mg/kg |
| **D3** | 1.8 mg/kg | 15 mg/kg | 1.8 mg/kg | 400 mg/kg | 400 mg/kg | 15 mg/kg |
| **D4** | 1.8 mg/kg | 15 mg/kg | 1.8 mg/kg | 400 mg/kg | 400 mg/kg | 15 mg/kg |
| **D5** | 1.8 mg/kg | 15 mg/kg | 1.8 mg/kg | 400 mg/kg | 400 mg/kg | 15 mg/kg |
| **D6** | 1.8 mg/kg | 15 mg/kg | 1.8 mg/kg | 400 mg/kg | 400 mg/kg | 15 mg/kg |
| **D7** | 1.8 mg/kg | 15 mg/kg | 1.8 mg/kg | 400 mg/kg | 400 mg/kg | 15 mg/kg |
| **D8** | 1.8 mg/kg | 15 mg/kg | 1.8 mg/kg | 400 mg/kg | 400 mg/kg | 15 mg/kg |
| **D9** | 1.8 mg/kg | 15 mg/kg | 1.8 mg/kg | - | - | 15 mg/kg |
| **D10** | 1.8 mg/kg | 15 mg/kg | 1.8 mg/kg | - | - | 15 mg/kg |
| **D11** | 1.8 mg/kg | 15 mg/kg | 1.8 mg/kg | - | - | 15 mg/kg |

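### Table 1 gives one nifurtimox dose for all patients in arms A and C, while the text sets a different dose for children under 15

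*Protocol*

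**What the plan says.** **Dose in the text.** The Nifurtimox paragraph of section 3.6 gives "15 mg/kg/day for 10 days in adults" and "20 mg/kg/day for 10 days in children under 15 years of age", in three daily doses.

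**Dose in the table.** Table 1 stands in the same section under Dosage by treatment group. Its rows for D2 to D8 read "1.8 mg/kg | 15 mg/kg | 1.8 mg/kg | 400 mg/kg | 400 mg/kg | 15 mg/kg", where the second and the last cells are nifurtimox in arms A and C. The last row reads "D11 | 1.8 mg/kg | 15 mg/kg | 1.8 mg/kg | - | - | 15 mg/kg". All ten rows show 15 mg/kg for nifurtimox. There is no row, column or footnote for children, and nothing limits the table to adults.

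**Who can be enrolled.** The inclusion criteria in section 3.2 ask for "written consent of the patient or of one of the parents/guardians for children under 15 years of age". The only limit on size or age in the exclusion criteria is a body weight under 10 kg.

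**Start day.** Section 3.5 treats D1 as the day treatment begins, and section 3.6 says "Patients will be treated from D1 onwards". Table 1 has its first row on D2. The Melarsoprol paragraph says "Treatment with prednisolone will start 24 hours before the beginning of the course of melarsoprol" and doses prednisolone from D1, in arms A and B only.

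**The concern.** Table 1 is the protocol's dosing schedule by arm, the page that staff are likely to consult or copy into working documents. For nifurtimox it conflicts with the paragraph just before it for a group of patients whom the protocol plainly allows into the trial. Nothing says which of the two prevails.

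Two things are at stake. The first is patient safety: a child's daily dose depends on which page is followed. The second is what the trial tests. Nifurtimox is in arms A and C and not in B. Until the two places agree, the regimen for children is defined in B and not in A or C, although failures and side effects are to be compared between arms in pairs.

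**Working it through.** The point rests on no power or sample size figure. The check is to compare Table 1 with the text, drug by drug.

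**Step 1. What a table cell means.** The eflornithine text gives 100 mg/kg every 6 hours, that is 4 × 100 = 400 mg/kg per day, and the table shows 400 mg/kg. The cells are therefore daily totals, and the nifurtimox cell of 15 mg/kg is a daily dose.

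**Step 2. Does the table otherwise reproduce the text?**

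| Drug | Text, section 3.6 | Table 1 | Agree? |
|---|---|---|---|
| Melarsoprol | 1.8 mg/kg/day, 10 days | 1.8 mg/kg, D2–D11 = 10 days | Yes |
| Eflornithine | 4 × 100 mg/kg/day, 7 days | 400 mg/kg, D2–D8 = 7 days | Yes |
| Nifurtimox, adults | 15 mg/kg/day, 10 days | 15 mg/kg, D2–D11 = 10 days | Yes |
| Nifurtimox, under 15 years | 20 mg/kg/day, 10 days | 15 mg/kg, D2–D11 = 10 days | **No** |

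Only the children's dose fails to match.

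**Step 3. Size of the gap for a child in arm A or C.** Course dose = daily dose × days.

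- Text: 20 × 10 = 200 mg/kg.
- Table: 15 × 10 = 150 mg/kg.
- Table relative to text: 150 / 200 = 0.75, so 25% less.
- Text relative to table: 200 / 150 = 1.33, so 33% more.

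For illustration, with an assumed weight of 20 kg, this is 400 against 300 mg per day, and 4,000 against 3,000 mg over the course.

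**Step 4. Start day.** Ten days from D1 end on D10 (1 + 10 − 1). Ten days from D2 end on D11 (2 + 10 − 1), as in Table 1. The course has ten days either way, so the mismatch moves it by one day and leaves the total dose unchanged. A prednisolone start on D1, 24 hours ahead of melarsoprol, puts melarsoprol on D2, in line with Table 1. The activity timetable in section 3.7 also appears to put the three combinations under D2–11, with only prednisolone on D1.

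**The case against.** **The table may be only a summary.** It is captioned as a timetable, has no age dimension and follows directly after the paragraph with the age split. The background in section 1.3 describes the same 15 and 20 mg/kg/day split, over two weeks, as the most widely used schedule. There is one centre, treatment is given in hospital, and section 5.2 provides for a written guideline, staff training and a one-month field test. All this makes confusion less likely. It does not remove the contradiction: the table does not say that it is for adults, and the dosing content of the guideline is not shown.

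**Bias.** A reader might infer that the conflict biases the comparisons of A with B and of B with C. The documents do not support that. It would require that children were in fact dosed inconsistently and that the difference changed cure or toxicity, and neither a direction nor a size can be derived. If the one centre follows one version throughout, dosing is uniform. Section 4.2 already collects the doses received, so a departure would be visible.

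**Number of children.** A reader might also want a count of those affected. The protocol gives no share of children. An assumed 20–40% of 145 per arm would be 29–58 (0.2 × 145 and 0.4 × 145), but nothing in the document supports that share. It would also count children exposed to the ambiguity, not children misdosed. The point does not rely on it.

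**Start day.** Taken literally, treatment from D1 might suggest that the 24-hour prednisolone lead cannot be kept. That reading does not survive. The Melarsoprol paragraph, Table 1 and the activity timetable together give one coherent schedule. The sentences in sections 3.5 and 3.6 name no trial drug. They can be read as prednisolone in arms A and B, or as the albendazole and antimalarial pre-treatment that all three groups receive, although no day is named for that. What stands is loose wording.

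**Conclusion.** The dose contradiction holds. For patients under 15 in arms A and C, the text and Table 1 differ by 50 mg/kg over the course (200 − 150), the table being 25% below the text. This rests only on figures printed in the protocol and on the fact that children of at least 10 kg are eligible. It is a patient-safety matter and leaves the tested regimen unfixed for children in two of three arms. It should be corrected whichever figure the clinical team intended; this review does not judge which is right.

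The start-day mismatch is secondary. No trial drug is scheduled on D1 in any arm in Table 1, so the sentences on treatment from D1 need aligning. The effect is a shift of one day at most, with no change in total dose and no bearing on the children's dose.

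**What to change.** 1. The clinical team should reconcile the Nifurtimox paragraph of section 3.6 with Table 1, so that both state the same dose by age group. They should then check that the written guideline named in section 5.2 carries the reconciled figures.
2. Align the D1 wording in section 3.5 and at the start of section 3.6 with the Melarsoprol paragraph, Table 1 and the activity timetable in section 3.7, saying what begins on D1 and what begins on D2 in each arm.

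The cost is a correction to the dosing paragraph, the table or both, and to two sentences. Sample size, visits and data collection are unaffected, since section 4.2 already records the doses received.

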***Dosage by treatment group***

**Table 1 : Timetable of treatment**

|  | **A** | | **B** | | **C** | |
| --- | --- | --- | --- | --- | --- | --- |
|  | **melarsoprol 1 inf / day** | **nifurtimox tabs 3/day** | **melarsoprol 1 inf / day** | **eflornithine 4 inf / day** | **eflornithine 4 inf / day** | **nifurtimox  tabs 3/day** |
| **D2** | 1.8 mg/kg | 15 mg/kg | 1.8 mg/kg | 400 mg/kg | 400 mg/kg | 15 mg/kg |
| **D3** | 1.8 mg/kg | 15 mg/kg | 1.8 mg/kg | 400 mg/kg | 400 mg/kg | 15 mg/kg |
| **D4** | 1.8 mg/kg | 15 mg/kg | 1.8 mg/kg | 400 mg/kg | 400 mg/kg | 15 mg/kg |
| **D5** | 1.8 mg/kg | 15 mg/kg | 1.8 mg/kg | 400 mg/kg | 400 mg/kg | 15 mg/kg |
| **D6** | 1.8 mg/kg | 15 mg/kg | 1.8 mg/kg | 400 mg/kg | 400 mg/kg | 15 mg/kg |
| **D7** | 1.8 mg/kg | 15 mg/kg | 1.8 mg/kg | 400 mg/kg | 400 mg/kg | 15 mg/kg |
| **D8** | 1.8 mg/kg | 15 mg/kg | 1.8 mg/kg | 400 mg/kg | 400 mg/kg | 15 mg/kg |
| **D9** | 1.8 mg/kg | 15 mg/kg | 1.8 mg/kg | - | - | 15 mg/kg |
| **D10** | 1.8 mg/kg | 15 mg/kg | 1.8 mg/kg | - | - | 15 mg/kg |
| **D11** | 1.8 mg/kg | 15 mg/kg | 1.8 mg/kg | - | - | 15 mg/kg |

## Treatment procedure

Patients included in the study will be hospitalised in the Arua HAT treatment centre throughout the treatment period.

## Side effects

In case of any side effect, the event will be recorded. The decision to withhold or to resume treatment will be left to the clinician in charge. Analysis will be done on an intention to treat basis.

The following definitions will be used for recording some of the side effects :

- Reactive encephalopathy: onset of a sudden or rapidly progressive episode of coma in a patient during treatment (Glasgow score less than or equal to 8) or status epilepticus.
- Arsobal reaction: tachycardia (pulse > 100 or 140 in children under 12 years of age), with fever > 38°C and conjunctival hyperaemia.
- Diabetes mellitus: fasting blood glucose greater than or equal to 1.3 g/l, associated with glycosuria.
- Cardiomyopathy: occurrence of an arrhythmia during treatment in a patient previously free from cardiovascular symptoms.
- Enteritis: occurrence of a diarrhoeic syndrome during treatment (three or more liquid stools per 24 hours, for three consecutive days or more) resistant to oral rehydration.

In case of occurrence of any manifestation that could lead to suspect imminent encephalopathy (severe headaches, conjunctival hyperaemia, high fever without a focus of infection or malaria parasites, isolated convulsion, behavioural disorders, etc.) the decision to withhold or to resume the treatment will be at the clinician’s discretion in accordance with the practices of the treatment centre.

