**Introduction**

*Trypanosoma brucei gambiense* (*Tbg*) Human African Trypanosomiasis (HAT) is a major public health problem in those areas in which it is currently rife (1). This is all the more so because the political upheavals, which disrupt the operations of the health services and cause population movements encourage the reappearance of historical foci (2,3). This disease, however, is still neglected and it is estimated that the control programmes cover only 10 to 20% of the 50 million people living in endemic regions (2).

HAT, which is consistently fatal in the absence of treatment, respond to a relatively non-toxic therapeutic agent, pentamidine(Pentacarinatâ), if the diagnosis is made at the hemo lymphatic phase (4). In the late stage of the disease, however, when the central nervous system is invaded by the parasite, use of arsenic derivatives such as melarsoprol (Arsobalâ) remains necessary. In about 5% of cases the use of melarsoprol causes iatrogenic encephalopathy, with a fatal outcome in up to 50%.

Eflornithine (difluoromethylornithine or eflornithine, Ornidylâ), for the time being, is the only other drug registered for the treatment of late-stage HAT. The institution of treatment regimens with eflornithine, however, is difficult because of the mode of administration of the product (1 infusion of 2 hours, every 6 hours). Actually, eflornithine is no longer available on the market but the patent is under supervision of WHO (5).

Nifurtimox (Lampitâ, Bayer), a product used in the treatment of Chagas disease, has only been tested empirically in HAT with contradictory results (4,6,7). This is a cheap drug, which is easy to administer (orally) but not registered for use in HAT. The type and frequency of side effects are poorly documented.

The available therapeutic spectrum for the treatment of late-stage HAT is therefore limited. Furthermore, the availability of the 3 drugs listed here is only guaranteed in the medium-term. Finally, signs of resistance to melarsoprol are beginning to appear in several areas (8,9).

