## Results and side effects of treatment with melarsoprol

In the late-stage disease, the cure rate after treatment with melarsoprol is estimated to be greater than 95% (10,11,14). The principal risk is that of reactive encephalopathy (5.9% of cases treated with melarsoprol in a series of 1083 patients in Zaire (15), with a high mortality rate (67.2% in the same series). In an Ivory Coast series with 350 patients (6), arsenical treatment was associated with minor side effects, such as isolated febrile episodes, pruriginous rashes and subcutaneous cellulitis, sometimes followed by necrosis at the injection site, in 11.4, 4.6 and 2.8% of cases, respectively.

MSF data from Adjumani in Northern Uganda provide the following figures: among 3110 late-stage patients treated with melarsoprol, 567 (18.2%) patients suffered side effects, including 194 (6.2%) cases of reactive encephalopathy. The lethality observed during treatment was 5.5% (170/3110). The lethality of reactive encephalopathies was 51.5% (100/194). The median duration of hospitalisation was 25 days (unpublished MSF data).

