## Early stopping rules

Every hundred patients included, the three treatment groups will be compared regarding :

- the lethality,
- the proportion of therapeutic failures at the end of hospitalisation, defined by the presence of trypanosomes in the CSF and/or the blood,
- the frequency of occurrence of serious adverse reactions

If the proportion of one of these events is significantly higher in one treatment group as compared to the other groups, the recruitment in this group will be stopped.

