**3.8. Analysis**

This will be an "intention-to-treat" analysis. The treatment groups will be compared pair-wise.

The first outcome variable is the proportion of therapeutic failures in each treatment group.

The second outcome variable is the proportion of side effects occurring in each group.

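### In an open trial, harms are recorded and counted as undefined 'side effects', so the safety outcome and one stopping comparison depend on attribution that may differ between arms

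*Protocol*

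**What the plan says.** Clinical safety is part of the main objective (section 2). Section 3.8 states: "The second outcome variable is the proportion of side effects occurring in each group". The groups are to be compared pair-wise. The early stopping rules in section 3.6 compare the groups after every hundred inclusions on three quantities, one of which is "the frequency of occurrence of serious adverse reactions". Recruitment to a group closes if its proportion is significantly higher.

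The recording rule is in section 3.6, under Side effects: "In case of any side effect, the event will be recorded". Five definitions follow, introduced by "The following definitions will be used for recording some of the side effects". One is "Arsobal reaction: tachycardia (pulse > 100 or 140 in children under 12 years of age), with fever > 38°C and conjunctival hyperaemia". The Introduction shows that Arsobal is melarsoprol: "use of arsenic derivatives such as melarsoprol (Arsobalâ) remains necessary". Another is reactive encephalopathy, defined by coma of abrupt or rapid onset with a Glasgow score of 8 or below, or by status epilepticus.

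Section 4.2 lists intercurrent disease among the clinical data and has a separate entry for side effects of treatment. The trial is open (sections 3.1 and 3.6, Blind), and programme doctors, clinical officers and nurses collect the data (section 4).

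**The concern.** A side effect, like an adverse reaction, is an event that someone has attributed to treatment. The protocol does not define either term or say who makes the attribution. In late-stage trypanosomiasis a convulsion, confusion, fever or headache can come from the disease, from another infection or from a study drug. The person deciding knows the arm.

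The protocol also states different expectations for each drug. Melarsoprol is linked to frequently fatal encephalopathy (section 1.1), eflornithine is described as better tolerated (section 1.3), and the side effects of nifurtimox are called poorly documented (Introduction). These expectations could lead staff to call the same sign a side effect in one arm and intercurrent disease in another.

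Two arms with equal true harm could then show different proportions in the second outcome, or real differences could be blurred. The same labelling feeds a rule that can close an arm. An event that was never written down cannot be recovered by a later analysis plan, so this cannot be left to the SAP.

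**Working it through.** **The passages side by side**

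1. Trigger for recording: a side effect, undefined (section 3.6).
2. Alternative category: intercurrent disease, listed separately (section 4.2). Sorting between the two is a causal judgement.
3. Knowledge of the arm: the trial is open. Section 5.1 concedes that without blinding, uniform treatment of patients across the groups is not guaranteed. It offers no safeguard for recording harms.
4. Use of the result: the second outcome and one of the three stopping comparisons.
5. Contrast with deaths: section 3.7 classifies the causality of a death as likely, unlikely or unknown, as a separate step. No such separation is stated for other events.
6. Definitions: two of the five are tied to melarsoprol in the document. One is the Arsobal reaction, by name. The other is reactive encephalopathy, which section 1.1 presents as that drug's main hazard: "The principal risk is that of reactive encephalopathy (5.9% of cases treated with melarsoprol in a series of 1083 patients in Zaire". Enteritis corresponds to the diarrhoea listed for eflornithine in section 1.3. Diabetes mellitus and cardiomyopathy are tied to no drug. All five are based on signs or tests, with no drug condition.

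**Size, as an assumed range**

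The protocol gives no figure for differential attribution, so there is nothing of its own to reproduce on this point. Inputs:

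- n = 145 per arm (section 3.3; 130/0.90 = 144.4, rounded up).
- True event rate p, equal in both arms: 18.2% from the Adjumani melarsoprol series (567/3110, section 1.1), and 30% as an assumption.
- Share of events attributed to treatment: 90% in one arm, 80% or 70% in the other. These are assumptions.

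Recorded rate = p × share attributed. The gap d is the difference in recorded rates. SE = √{[r₁(1−r₁) + r₂(1−r₂)]/145}. The chance of a two-sided 5% result is Φ(d/SE − 1.96) + Φ(−d/SE − 1.96).

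Worked row, p = 18.2%, 90% v 70%: r₁ = 0.182 × 0.9 = 0.1638 and r₂ = 0.182 × 0.7 = 0.1274, so d = 0.0364. SE = √{(0.1638 × 0.8362 + 0.1274 × 0.8726)/145} = 0.0414, and d/SE = 0.88. The probability is Φ(−1.08) + Φ(−2.84) ≈ 0.14.

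| True rate | Attribution | Recorded rates | False gap | Chance of p < 0.05 |
|---|---|---|---|---|
| 18.2% | 90% v 80% | 16.4% v 14.6% | 1.8 points | about 7% |
| 18.2% | 90% v 70% | 16.4% v 12.7% | 3.6 points | about 14% |
| 30% | 90% v 80% | 27% v 24% | 3 points | about 9% |
| 30% | 90% v 70% | 27% v 21% | 6 points | about 22% |

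With equal attribution the chance is 5%. The table is symmetric: it does not say which arm would be under-recorded.

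**The case against.** The strongest reply is that much of the raw information is collected without attribution. Section 4.2 records temperature, neurological signs and intercurrent disease during hospitalisation, and the timetable of activities in section 3.7 schedules clinical evaluation on D2–11 and D12 in every arm. This stands in part: a fever or neurological sign has a place in the record whatever its presumed cause. But those fields feed no stated outcome, so attribution still decides what is counted. Vomiting or a rash, for instance, has no field of its own in that list.

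Several stronger readings are tempting, and the documents do not support them.

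- *That an unblinded clinician alone decides what is recorded.* Section 3.6 names no assessor of side effects. The clinician in charge is named only for decisions to withhold or resume treatment.
- *That the definitions as a set are modelled on melarsoprol.* Only two of five are tied to it, and the list expressly covers only some side effects.
- *That the Arsobal signs have no label in arm C.* The criterion is pulse, temperature and conjunctival hyperaemia and can be applied there. The weakness is the name, and the absence of any statement that it applies in every arm.
- *That undefined effects of eflornithine and nifurtimox separate A and B from C.* Nifurtimox is given in A and C, eflornithine in B and C, so the missing definitions do not fall on arm C alone.
- *That about two thirds of side effects are unclear events,* because 373 of 567 (567 − 194) Adjumani patients with side effects are not accounted for by encephalopathy. Section 1.1 does not break those patients down, so this cannot be inferred.

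It is also fair that lethality, another of the stopping criteria, needs no causal judgement, and that counting all events does not remove unblinded detection.

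**Conclusion.** The point holds as a weakness in how the safety outcome is fixed. Both the recording rule and the counting rule rest on an undefined causal label, applied by staff who know the arm, and the document contains no safeguard. The second outcome and the serious-reaction stopping comparison may therefore reflect attribution as well as harm.

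A reader might infer that the comparisons of A and B with C are biased against melarsoprol. The documents establish neither that a bias will occur nor its direction, only that the plan leaves room for one.

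The size is illustrative: false gaps of 1.8 to 3.6 points at the protocol's 18.2% rate and 3 to 6 points at an assumed 30%, with false significance in about 7% to 14% and 9% to 22% of trials. These figures assume equal true rates, the stated attribution shares and 145 evaluable patients per arm. They describe the final pair-wise comparison, not the interim looks. The sample size is unaffected.

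**What to change.** - **Section 3.6, Side effects:** record every new or worsened clinical event from D1 in all arms, whatever its suspected cause, with its seriousness. Keep causality as a separate field.
- **Section 3.8:** define the second outcome as the proportion of patients with at least one such event, and the proportion with at least one serious event, regardless of attribution. Keep the attributed analysis as secondary.
- **Early stopping rules:** compare serious adverse events of any cause in place of serious adverse reactions.
- **Definitions:** give the Arsobal reaction a drug-neutral name and state that all five definitions apply in all three arms.

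The cost is changed wording and more form entries, made at evaluations already scheduled. All-cause rates will be higher and will include disease symptoms, which slightly dilutes the contrast between arms. The secondary attributed analysis keeps the narrower view available.

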**2. Objectives**

## Main objective

To compare the following three therapeutic combinations in terms of therapeutic efficacy and clinical safety: A: [melarsoprol + nifurtimox], B: [melarsoprol + eflornithine] et
C: [eflornithine + nifurtimox] in patients suffering from *Tbg* HAT in the meningo-encephalitic phase.

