**3. Methods**

**3.1. Study design**

Open, randomised, clinical equivalence trial

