## Patients withdrawal during the treatment

Patients will be withdrawn if :

- A deviation from treatments schedules is made by patients’ voluntary abandon.
- Exclusion criteria occurs at post-inclusion (see paragraph exclusion criteria in 3.2)

Patients will continue to receive the same treatment and follow-up will be done. These patients will be excluded from the analysis.

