**4.2. Data to be collected**

*Demographic data:*

Name, age, sex, address, screening method (active or passive).

*Laboratory data on inclusion:*

Result of CATT whole blood and 1/4 dilution

Results of lymph node puncture (trypanosome +/‑)

Results of parasitological examination of the blood (WOO +/‑; QBC +/‑)

Results of parasitological examination of the CSF (trypanosome +/‑)

Spinal cell count

Haematology

*Clinical data on inclusion and during hospitalisation:*

Disease history

Weight/height on admission

Weight on discharge

Temperature

Lymph nodes

Neurological signs

Intercurrent disease

Treatment received and doses

*Side effects of treatment*

*Results of treatment*

*Laboratory data on discharge:*

Results of parasitological examination of the blood (QBC +/‑)

Parasitological examination of the CSF (trypanosome +/‑)

Spinal cell count

Haematology

Specific IgM in CSF and serum (Antwerp)

*Laboratory data during follow-up:*

Results of lymph node puncture (trypanosome +/‑)

Results of parasitological examination of the blood (QBC +/‑)

Parasitological examination of the CSF (trypanosome +/‑)

Spinal cell count

Specific IgM in CSF and serum (Antwerp)

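### Intention to treat is the only analysis named for an equivalence claim, although clinicians may withhold treatment; this can, but need not, raise the false-equivalence rate, so a per-protocol analysis should be required alongside it

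*Protocol*

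**What the plan says.** Section 3.1 describes the design as "Open, randomised, clinical equivalence trial". The arms are combinations, "A: [melarsoprol + nifurtimox], B: [melarsoprol + eflornithine"] and C, eflornithine with nifurtimox. Each pair of arms therefore has one drug in common: melarsoprol for A and B, nifurtimox for A and C, eflornithine for B and C.

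Section 3.6 (Side effects) states that the choice to withhold or resume treatment "will be left to the clinician in charge. Analysis will be done on an intention to treat basis". It gives the clinician the same freedom when encephalopathy is only suspected. Section 3.8 opens with "This will be an 'intention-to-treat' analysis" and continues "The treatment groups will be compared pair-wise". No per-protocol or as-treated set is named.

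Section 3.6 (Patients withdrawal during the treatment) lists two groups: patients who abandon treatment voluntarily and patients who meet an exclusion criterion after inclusion. Of these it says "These patients will be excluded from the analysis". Patients whose treatment the clinician withholds are in neither group, so they stay in the analysis.

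Section 4.2 already lists "Treatment received and doses" among the data collected in hospital.

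**The concern.** Under a superiority aim, incomplete treatment usually works against the claim, and intention to treat is the cautious choice. Under an equivalence aim it is not reliably cautious, because anything that narrows the contrast between arms favours the claim.

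The shared-drug design gives this a concrete route. Suppose melarsoprol is stopped in a patient in arm B and nifurtimox in a patient in arm C. Both are then on eflornithine alone, yet intention to treat counts them as evidence about two different combinations. A similar pull arises if only the better arm loses treatment. At stake is the 5% risk of a wrong equivalence claim stated in section 3.3.

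**Working it through.** **Inputs from the protocol.** Cure rate 95%, margin 10 points, one-sided alpha 5%, power 80%, 130 per group, 145 after 10% drop-out (3.3). A 90% confidence interval for the difference (3.8, Multivariate analysis). On melarsoprol in Adjumani, 6.2% had reactive encephalopathy and 18.2% had any side effect (1.1). In Arua, about 25% of first full courses of melarsoprol fail, so about 75% succeed (1.2).

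**Assumptions.** The protocol gives no withholding rate, so I let the share w with a drug withheld run from 6.2% to 18.2%. These are side-effect rates on melarsoprol alone, so they are only a guide, and a weaker one for arm C. I take 75% as the cure rate on the remaining drug. Each event is treated as complete loss of that drug.

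**The plan's own figure.** For 95% v 85%, with mean 0.90:

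n′ = [1.645·√(2·0.90·0.10) + 0.842·√(0.95·0.05 + 0.85·0.15)]² / 0.10² = (0.698 + 0.352)² / 0.01 = 110.3

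With the continuity correction, n = (n′/4)·[1 + √(1 + 4/(0.10·n′))]² = 129.5, so 130. Then 130/0.90 = 144.4, so 145. Both stated figures reproduce.

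**Method.** I enumerated all pairs of binomial outcomes at 130 per arm and summed the probability of those where the 90% interval, d ± 1.645·√[pA(1−pA)/n + pB(1−pB)/n], lies wholly within ±10 points. Full-treatment cure rates are 95% and 85%, exactly at the margin. An affected arm's cure rate becomes (1−w)·(full-treatment rate) + w·(rate on the remaining drug). For example, at w = 6.2% the better arm is 0.938·95% + 0.062·75% = 93.76%.

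With nothing withheld, the false-equivalence rate is 5.6%.

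| Who loses which drug | w = 6.2%: cure rates (difference) | Rate | w = 18.2%: cure rates (difference) | Rate |
|---|---|---|---|---|
| Both arms, unshared drug | 93.76 v 84.38 (9.38) | 7.5% | 91.36 v 83.18 (8.18) | 12.0% |
| Better arm only | 93.76 v 85.00 (8.76) | 10.1% | 91.36 v 85.00 (6.36) | 23.5% |
| Worse arm only | 95.00 v 84.38 (10.62) | 4.0% | 95.00 v 83.18 (11.82) | 2.0% |
| Both arms, shared drug; drugs left cure 85% v 75% | 94.38 v 84.38 (10.00) | 5.6% | 93.18 v 83.18 (10.00) | 5.5% |
| Both arms, shared drug; drugs left cure 85% v 60% | 94.38 v 83.45 (10.93) | 3.3% | 93.18 v 80.45 (12.73) | 1.2% |

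**Sensitivity.** Checking only the upper limit, as section 3.8 words its rule, changes little: 7.6% and 12.2% in the first row. Letting the shared drug alone cure 60% to 95% in the first row gives 7.4% to 7.8% at w = 6.2%, and 10.6% to 14.0% at w = 18.2%. The shared-drug rows depend on the two drugs left differing by at least as much as the combinations do; if those drugs cured equally well, the pull toward equivalence would return.

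**Power of the added analysis.** For 95% v 95% with both limits required, exact power of the per-protocol interval is 94.8% at 130 per arm, 93.4% at 122 (6.2% removed), 92.6% at 117 (10% removed) and 89.5% at 106 (18.2% removed).

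**The case against.** Several points on the other side stand.

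- **One drug or both.** A reader might infer that the clinician stops one drug and leaves the other. Section 3.6 speaks only of treatment, and of resuming it. If the whole combination is paused, no one is left on the shared drug and that mechanism does not arise, although the contrast between full regimens may still be diluted.
- **Direction.** A reader might infer that withholding always makes arms alike, or that a more toxic arm is always easier to call equivalent. The documents do not support this. In A v B, melarsoprol is the shared drug; stopping it leaves nifurtimox against eflornithine. In A v C and B v C, stopping melarsoprol affects one arm only, so the effect depends on which arm is better. Deaths likely due to treatment count as failures (3.7), and an arm with significantly more deaths or serious reactions stops recruiting (3.6), so toxicity can also separate arms.
- **Target.** The hypotheses in 3.3 do not require a full course. If the question is the policy of starting a combination, a true 9-point difference lies inside the margin and accepting it is no error. The rates above are errors only against the full-treatment difference.
- **Selection.** A per-protocol set is chosen after randomisation, by toxicity that may differ between arms, so it carries its own bias.

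A supportive set may also sit in an analysis plan that is not shown. That does not settle the matter: the protocol names intention to treat twice, once for exactly these patients, and writes its equivalence rule in 3.8 with no second set. Nor do the exclusions for withdrawal (3.6) and for deaths judged unrelated or of unknown cause (3.7) create a per-protocol set. They conflict with intention to treat, but that is a separate point.

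**Conclusion.** The point holds in a limited form. Intention to treat as the sole named basis for an equivalence claim, with discretionary withholding in an open trial, can raise the false-equivalence rate above the stated 5%. From a baseline of 5.6%, it rises to about 7.5% to 12% if both arms lose the unshared drug and about 10% to 23% if only the better arm loses treatment. It falls to 4.0% to 2.0% if only the worse arm does, and is unchanged or lower in the shared-drug cases worked.

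These sizes rest on the assumed 6.2% to 18.2% withheld, the assumed 75% cure on the remaining drug, and a full-treatment target. It would be too strong to say that the error rate does exceed 5%. Because the direction cannot be known in advance, a second analysis set is needed to expose it. This should be changed, but it does not invalidate the design.

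**What to change.** In section 3.8:

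1. Add a per-protocol analysis of patients who received the planned course of both drugs, defined from the dose data in 4.2. Keep deaths and failures during treatment in this set as failures, so that it cannot hide toxicity.
2. State how a patient whose treatment was withheld, in part or in full, is classified, and report their number by arm.
3. Allow an equivalence claim only if the intention-to-treat and per-protocol 90% intervals both lie within ±10 points.
4. Keep superiority and safety conclusions on intention to treat.

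The cost is one more analysis of data already collected, with no change to patient care. Equivalence becomes slightly harder to claim: per-protocol power is about 93% at 117 per arm and 89% at 106, still above the planned 80%. Joint power cannot exceed the lower of the two analyses, and will be lower still if withholding in one arm opens a real intention-to-treat difference. Because the per-protocol set is open to selection, it supplements intention to treat and does not replace it.
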